# Standard Best Supportive Care

All subjects enrolled in this clinical study should always receive Standard Best Supportive Care (SBSC). SBSC is defined by the institutional standards of the participating clinical centers. In general, SBSC has to be understood as the multi-professional attention to the patient’s overall physical, psychosocial, spiritual, and cultural needs available at all stages of the illness. Regarding the physical well-being of HCC subjects enrolled in this trial, SBSC may include but may not be restricted to: (i) blood transfusion for anemic state; (ii) antibiotics to control infections; (iii) analgesics, including non-steroidal anti-inflammatory drugs, opioids, and corticosteroids; (iv) antiemetic drugs; (v) vitamin and nutritional support and; (vi) alternative medicine (include herbal medicine) are allowed except of those have any statement of "anticancer activity" or "immunologic activity" in the labels. Localized radiation therapy to alleviate symptoms such as pain due to non-target lesions is allowed according to institutional standards. Other palliative care will be also provided to the best interest of a subject is receiving study drug.

# Study Population

Pathologically confirmed hepatocellular carcinoma with extrahepatic metastasis at the Eastern Hepatobilliary Surgery Hospital, Zhejiang Sian Hospital and Fujian Provincial Cancer Hospital.

## 5.1 Inclusion Criteria

1. Male and female, ages 18-75 and above, with documented advanced HCC
2. Child-Pugh Class A.
3. With confirmed extrahepatic metastatic lesions located in bone, lung, abdominal metastasis including lymph nodes.
4. ECOG performance status Grade 1 or less.
5. Liver and renal lab test must meet the following ranges:
   1. Total bilirubin equal or less than 1.5 times of upper normal limit (UNL) defined by each clinical lab in each site.
   2. ALT and AST less than 2.5 times of times of upper normal limit (UNL) defined by each clinical lab in each site.
   3. Serum Creatinine equal or less than 1 times of upper normal limit (UNL) defined by each clinical lab in each site.
   4. Endogenous creatinine clearance rate >50ml/min (calculated with Cockcroft-Gault formulation).
6. Other lab tests:
   1. Hemoglobin >= 90g/L
   2. Platelet Count >=75 ˟10 ^9^/L
   3. WBC Count >=3.5 ˟10 ^9^/L
7. Good cardiac function, no myocardial infarction within 6 months; well controlled hypertension and coronary heart disease if any.

## 5.2 Exclusion Criteria

1. No extrahepatic metastatic lesion found.
2. Decompensated liver function or hepatic encephalopathy.
3. Pregnant or breast-feeding women.
4. Uncontrolled hypertension even with medication.
5. Patients with hemorrhagic disorders or active bleeding or sepsis
6. History of HIV infection and AIDS or other acute or chronic disease.
7. Active or uncontrolled severe infections.
8. CHF NYHA class > 2, active CAD or cardiac ischemia, uncontrolled cardiac arrhythmias even with anti-arrhythmic therapy.
9. Unable to take oral medication.
10. Low compliance judged by investigators.
11. Seizure disorder requiring medication (such as steroids or anti-epileptics).
12. History of drug abuse, or mental disorders which could compromise compliance.
13. Any other conduction which may jeopardize patient safety and compliance.

# Informed Consent

The Investigator must ensure that written informed consent to participate in the study is obtained before including any individual as a subject in the study, and before conducting any study-related assessments. The investigator must provide the prospective subject, or the prospective subject’s legally authorized representative, with sufficient opportunity to consider whether to participate, and minimize the possibility of coercion or undue influence. The process is designed to 1) give the subject all the information that he/she needs, 2) ensure that the subject understands the information and 3) give the subject a chance to consider study participation. The process should permit the subject to ask questions and exchange information freely.

Specifically, the Investigator is to explain to each subject all elements of informed consent as specified by CFDA. This also includes explaining that photographs will be taken and may be used in publications in ways that do not identify the subject. After the explanation, the subject or legally authorized representative will voluntarily sign and date the consent/assent form if they wish to participate in the study. A copy of the consent/ assent form must be provided to the subject or the subject’s legally authorized representative. A signed and dated copy of the consent/assent form must be always maintained in the Investigator Site File. The informed consent process must be followed, and the subject’s participation in the study, must be documented in the subject’s medical record/chart.

# Endpoints and Assessment

## 7.1 Primary Endpoint

Overall Survival (OS): OS is defined as the time from randomization to the time of death from any cause. Subjects who are alive at the time of the final analysis or who have become lost to follow-up will be censored at their last known alive date.

## 7.2 Secondary Endpoints

Progression Free Survival (PFS): PFS is defined as the time (in months) from randomization to the time of radiographic disease progression. Subjects without progression will be censored at their last tumor assessment date. Subjects who have no on-study tumor assessments will be censored at the date of randomization.

Objective Response Rate (ORR): ORR is defined as the proportion of randomized subjects in each treatment arm whose best response is a CR or PR using the modified RECIST for HCC.

Disease Control Rate (DCR): DCR is defined as the proportion of randomized subjects in each treatment arm whose best response is a CR, PR or SD using the modified RECIST for HCC.

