# Study Objectives

1. To determine whether ATRA + FOLFOX can improve the overall survival, progress-free survival, time to progress, symptomatic progress, and health-related quality of life.
2. To determine the safety of ATRA in the combination with FOLFOX.

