**9.2 Populations for Analysis**

Intent-to-treat (ITT) population: any patients assigned to a treatment group by the randomization process, regardless of whether patients received any study treatment or received a different study treatment from which they were randomized. This is the primary data set for the test of overall survival, analyses of secondary efficacy endpoints like TTP, symptom assessment and baseline characteristics.

Per protocol (PP) population: all randomized subjects except for subjects who 1) have wrong diagnosis of cancer; 2) are not treated; 3) are not treated with the study therapy as assigned by the randomization. This is the primary dataset for the test of overall survival.

Safety population: All subjects who received at least one dose of study medications. This is the primary data set for dosing, safety, concomitant medications.

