**1.3 Secondary hypothesis**

- ATRA-FOLFOX4 leads in HCC patients with EHM compared to FOLFOX4 alone to better progress-free survival.
- To determine the safety of ATRA in the combination with FOLFOX

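### PFS counts radiographic progression only, so the SAP's PFS hypothesis would be tested on what is in effect time to progression

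*Combined protocol and SAP*

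**What the plan says.** Protocol 7.2 (Secondary Endpoints) and SAP 4.2 (Secondary outcome) word the endpoint identically: "PFS is defined as the time (in months) from randomization to the time of radiographic disease progression". Two censoring rules follow: "Subjects without progression will be censored at their last tumor assessment date", and "Subjects who have no on-study tumor assessments will be censored at the date of randomization". Neither rule makes an exception for a patient who has died.

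Death is named as an event only for the primary endpoint, in protocol 7.1 and SAP 4.1: "OS is defined as the time from randomization to the time of death from any cause". The table of response definitions after protocol 7.3 describes progressive disease by lesion findings only.

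The Study Objectives list "progress-free survival, time to progress, symptomatic progress" as separate items. Protocol 9.2 and SAP 2.2 refer to "analyses of secondary efficacy endpoints like TTP, symptom assessment and baseline characteristics". TTP has no definition in either document.

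PFS is the only efficacy item in SAP 1.3: "ATRA-FOLFOX4 leads in HCC patients with EHM compared to FOLFOX4 alone to better progress-free survival". SAP 5.2 tests it by log-rank at the 5% level with Kaplan-Meier curves under ITT, and provides no competing-risk method.

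**The concern.** Progression-free survival ordinarily ends at progression or death, whichever comes first. Here a patient who dies without documented progression falls under the rule for subjects without progression and is censored. If death comes before any scan, censoring is on day 0 and the patient contributes neither an event nor follow-up time, although the analysis is called ITT. ORR and DCR treat such a patient differently: their denominator is all randomized subjects.

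Two things are at stake. First, a statement that ATRA improves PFS would rest on progression alone. Secondly, Kaplan-Meier medians labelled PFS would be longer than medians that count death. If deaths without progression differ between arms, the hazard ratio would not be the PFS hazard ratio either.

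**Working it through.** **1. Reading the rules case by case**

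| Patient | As written | Progression or death |
|---|---|---|
| Progresses, later dies | Event at progression | Same |
| Alive, no progression | Censored at last scan | Same |
| Scanned, dies without documented progression | Censored at last scan | Event at death |
| Dies before any scan | Censored on day 0 | Event at death |

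Only the last two rows differ. No sentence states that deaths are censored, but the rules lead nowhere else.

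**2. The plan's own figure**

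The documents give no PFS median, event count or power. The only size figure is 106 patients, based on OS (protocol 9.1, SAP 1.6). It reproduces as follows:

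- HR = 8.2/14.9 = 0.550.
- Freedman events = (1.960 + 0.842)² × [(1 + 0.550)/(1 − 0.550)]² = 93.3 with the unrounded HR, so 94, or 47 per arm.
- 47/0.90 = 52.2, so 53 per arm and 106 in total.

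This match treats required events as patients. For the present point it shows only that the sample size does not depend on PFS.

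**3. Deaths before a first scan at 4 weeks**

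The assumption is exponential OS at the design medians. Four weeks is 28/30.4375 = 0.92 months.

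- Control: 1 − 2^(−0.92/8.2) = 7.5%, about 4 of 53.
- ATRA: 1 − 2^(−0.92/14.9) = 4.2%, about 2 of 53.

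This is an order of magnitude only. A constant hazard from day 0 may overstate early deaths in patients selected for good liver function and performance status.

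**4. Effect on the median**

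Let λ be the constant hazard of a first event (progression or death) and q the share of first events that are deaths without progression. Censoring those deaths leaves hazard (1 − q)λ, so the reported median is the true PFS median divided by (1 − q). The events lost, if all 106 patients had a first event, are 106q.

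| q (assumed, both arms) | Median multiplied by | Events lost |
|---|---|---|
| 5% | 1.05 | 5 |
| 10% | 1.11 | 11 |
| 20% | 1.25 | 21 |
| 30% | 1.43 | 32 |

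The factor is approximate, because the plan censors at the last scan and not at death.

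**5. Effect on the hazard ratio**

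With control share q, true PFS HR = (1 − q) × HR(progression) + q × HR(death without progression). Take q = 20% and a progression HR of 0.65, both assumed. The plan as written reports 0.65 in every row.

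| HR for death without progression | True PFS HR |
|---|---|
| 0.55 (the design OS ratio) | 0.52 + 0.11 = 0.63 |
| 0.65 | 0.52 + 0.13 = 0.65 |
| 1.5 (assumed adverse case) | 0.52 + 0.30 = 0.82 |

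Equivalently, HR as written = true PFS HR × (1 − q in ATRA)/(1 − q in control). For a true PFS HR of 1.00:

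- q of 20% on ATRA and 10% on control: 0.80/0.90 = 0.89.
- q of 30% and 10%: 0.70/0.90 = 0.78.
- q of 10% and 20%: 0.90/0.80 = 1.13.
- Equal q: 1.00, no change.

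**The case against.** The strongest reply is that this is a labelling matter in a secondary endpoint. PFS carries no power claim, the 106 patients rest on OS, and OS counts every death under ITT. That stands, and it limits the severity.

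The group affected may also be small. Scans are every 4 weeks, the progression criteria are broad (including any new extrahepatic lesion and intrahepatic growth), and eligibility requires Child-Pugh A and ECOG 1 or less. That is reasonable, but the documents give no count of deaths without progression, so it cannot be confirmed.

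On the plan's own OS ratio the hazard ratio hardly moves (0.63 against 0.65), and the written definition is then slightly conservative against ATRA. That also stands. The 0.82 case needs ATRA to raise deaths without progression by half, which nothing in the documents suggests.

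Finally, adding death to the event brings its own difficulty. The Schedule of Events ends at M12, while survival follow-up continues until the required number of events. A death long after the last scan would then become a late PFS event after an unobserved interval. The fix has to deal with this.

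None of these replies makes the present variable progression-free survival.

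**Conclusion.** The definition should be corrected. As written, the endpoint called PFS is in effect time to progression, and the SAP 1.3 hypothesis would be tested on it. Relative to true PFS, medians are too long whenever q is above zero, by about 1.11 to 1.43 times for q of 10% to 30%. That range assumes constant hazards and an assumed q. The direction of any change in the hazard ratio is unknown, and the change is about nil if q is equal in both arms.

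A reader might infer more than the documents support:

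- **That the worst outcomes are removed, or early deaths ignored.** Only deaths without documented progression are lost, only from this endpoint, and all of them count in OS.
- **That the definition favours ATRA.** It can shift the hazard ratio either way.
- **That PFS is the main secondary endpoint.** It is listed first and is the only efficacy item in SAP 1.3, but the documents do not rank the secondary endpoints.
- **That PFS and TTP are proven to be the same variable.** TTP is undefined, so this cannot be verified.
- **That Table S2 settles the matter.** It is labelled DFS and does not define its event, so it neither confirms nor removes the problem.

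Severity is should-fix: a secondary endpoint with no stated power, but one that carries a hypothesis.

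**What to change.** In both protocol 7.2 and SAP 4.2:

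1. Define PFS as time from randomization to the earlier of radiographic progression and death from any cause.
2. Censor patients who are alive without progression at their last tumor assessment.
3. Censor patients with no on-study assessment at randomization only if they are not known to have died.
4. Keep the present definition under the name TTP, so that the separate mentions in the Study Objectives, protocol 9.2 and SAP 2.2 have a meaning.

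In SAP 5.2, report the number of deaths without documented progression by arm. Add a sensitivity analysis for deaths that follow a long gap without scans, with the length of gap stated in advance.

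The cost is a few sentences in each document, one re-derived variable and one extra analysis. Death dates are already collected for OS, and the sample size does not change. The downside is that reported PFS medians will be somewhat shorter.

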## 7.3 Safety Endpoints

Study drug toxicities will be assessed continuously, which include vital sign, physical exam, neurological exam, EKG, Echo, clinical lab tests (hemoglobin, hematocrit, red blood cell, total leukocyte count with differential, platelet count, AST, ALT, total bilirubin, direct bilirubin, alkaline phosphatase, lactate dehydrogenase (LDH), creatinine, BUN or urea, blood glucose, total protein, albumin, sodium, potassium, chloride, total calcium, phosphorus, magnesium, ammonia, and AFP) and specialty exams (chest X-ray, CT, MRI, Bone Scan, etc.). All the adverse events will be evaluated according to the NCI CTCAE (Version 4.0), on a continuous basis while the subject is on study. Scheduled evaluations will occur every 4 weeks.

| **Parameters** | **Definitions** |
| --- | --- |
| **Complete Response (CR)** | Complete disappearance of extrahepatic metastatic lesions under the contrast-agent enhancement in the arterial phase of spiral CT or MRI. CR must be confirmed by a second evaluation no less than 4 weeks after the date the CR was first obtained. |
| **Partial Response (PR)** | Decrease of > 30% in the sum of the longest diameters (SLD) of extrahepatic metastatic lesions taking reference the baseline SLD. PR must be confirmed by a second evaluation no less than 4 weeks after the date the PR was first obtained. |
| **Stable Disease (SD)** | Failure to meet criteria for complete or partial response, in the absence of progressive disease. |
| **Progressive Disease (PD)** | - Increase of > 20% in the SLD of extrahepatic metastatic lesions taking reference the smallest SLD of target lesions recorded since the treatment started. If the 20% or more increase is observed in two consecutive determinations, the date of PD is the date of the first evaluation. OR - New extrahepatic metastatic lesions with the longest diameter of at least 10 mm confirmed by contrast-enhanced spiral CT or MRI imaging. OR - Appearance of one or more new extrahepatic lesions of any size. OR - Appearance of more intrahepatic lesions, expanding existing lesions (including portal vein emboli). |
|  |  |

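### The response table gives no threshold for liver growth, no rule for a scan that meets both response and progression, and no link to the modified RECIST criteria named for ORR and DCR

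*Combined protocol and SAP*

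**What the plan says.** Protocol section 7.2 and SAP section 4.2 define ORR as the proportion of randomized subjects "whose best response is a CR or PR using the modified RECIST for HCC". DCR names the same criteria. Protocol Study Design says that progression is determined by them too, with tumour evaluation every 4 weeks. Neither document sets these criteria out.

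A response table with no title follows in protocol section 7.3, Safety Endpoints. Its rows are:

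- **CR:** "Complete disappearance of extrahepatic metastatic lesions under the contrast-agent enhancement in the arterial phase of spiral CT or MRI".
- **PR:** "Decrease of > 30% in the sum of the longest diameters (SLD) of extrahepatic metastatic lesions taking reference the baseline SLD".
- **SD:** "Failure to meet criteria for complete or partial response, in the absence of progressive disease".
- **PD**, any one of four items:
  - "Increase of > 20% in the SLD of extrahepatic metastatic lesions taking reference the smallest SLD of target lesions recorded since the treatment started";
  - "New extrahepatic metastatic lesions with the longest diameter of at least 10 mm confirmed by contrast-enhanced spiral CT or MRI imaging";
  - "Appearance of one or more new extrahepatic lesions of any size";
  - "Appearance of more intrahepatic lesions, expanding existing lesions (including portal vein emboli".

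CR and PR each need confirmation at least 4 weeks later. The SAP sections available to us do not repeat the table.

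**The concern.** The response rows and the progression row look at different disease. Patients have hepatocellular carcinoma, yet the liver does not enter CR or PR, so a patient with persisting liver tumour can be a complete responder. The liver does enter PD, through an item that a reader cannot apply consistently.

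These categories appear to feed every listed secondary efficacy endpoint (PFS, ORR and DCR). The supplementary proteomics models also group patients by PD, SD, PR and CR. If the table is followed as written, two careful readers can give the same patient a different best response or progression date, and one scan can count on both sides. That goes beyond missing detail, because the secondary endpoints would not be consistent with one another.

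**Working it through.** The documents give no figure on this point to reproduce. The check is a side-by-side reading, followed by two short calculations.

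**1. Lesions counted and thresholds**

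| Category | Extrahepatic | Intrahepatic | Excludes PD? |
| --- | --- | --- | --- |
| CR | complete disappearance | not counted | not stated |
| PR | sum falls >30% from baseline | not counted | not stated |
| SD | neither CR nor PR | only through PD | yes |
| PD | sum rises >20% over smallest, or new lesion | more lesions, or expansion with no percentage, millimetre limit or reference scan | n/a |

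**2. Overlap.** Take a scan on which the metastases have shrunk by more than 30% and a liver lesion is larger. It meets PR and it meets PD. SD is ruled out, but nothing rules out PR. Confirmation narrows the overlap without closing it: the confirming scan can itself be the PD scan, and the confirmation wording does not mention PD. The patient is then a responder for ORR and DCR and a PFS event on the same scan.

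**3. New extrahepatic lesions.** The items are joined by OR. One requires at least 10 mm and the next accepts any size. Any lesion meeting the first also meets the second, so the 10 mm limit has no effect.

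**4. Other wording in the PD row.** The growth item says >20% and then, for two consecutive determinations, 20% or more. It compares extrahepatic lesions with the smallest sum of target lesions, without saying that these are the same set. The expansion clause is not expressly confined to the liver. If it covers all lesions, it conflicts directly with the >20% rule.

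**5. Effect of having no threshold (illustration).** Assume an unchanged liver lesion, independent continuous measurement error on each scan, and any larger reading called expansion. With a baseline scan and *k* follow-up scans:

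- Against baseline, no call is made only if baseline is the largest of *k*+1 readings. P(false PD) = 1 − 1/(*k*+1), which is 50%, 67% and 75% for *k* = 1, 2, 3.
- Against the smallest earlier value, no call is made only if the readings fall in strict order. P(false PD) = 1 − 1/(*k*+1)!, which is 50%, 83% and 96%.

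Neither result depends on the size of the error. Under a >20% rule against the smallest earlier value it does. Simulated values by the third scan are about 0% at 3% error, 2.7% at 5%, 15% at 7% and 37% at 10%.

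The literal reading is an extreme. If diameters are recorded to whole millimetres (assumed lesion 20–50 mm, error 3–10%), the third-scan figures become 50–72% against baseline and 72–94% against the smallest earlier value.

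**6. Direction of the effect on ORR.** Let *f* be the extrahepatic share of the baseline sum over all lesions, *a* the proportional fall in extrahepatic lesions and *b* the fall in liver lesions. The all-disease fall is *fa* + (1 − *f*)*b*. Apply the table's 30% to that sum, as an assumption:

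- Metastases gone, liver unchanged (*a* = 1, *b* = 0): the fall is *f*. The patient is no longer a CR but remains a PR if *f* > 0.30.
- Metastases shrunk by more than 30%, liver unchanged: a response is lost if *fa* ≤ 0.30.
- Metastases shrunk by no more than 30%, liver shrunk more: a response is gained if *fa* + (1 − *f*)*b* > 0.30.

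ORR can therefore move either way. CR cannot: every whole-disease CR is also a CR under the table, so the table's CR count is equal or higher.

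**The case against.** **The extrahepatic focus may be deliberate.** The trial enrols HCC with extrahepatic metastasis, the inclusion criteria do not require measurable liver tumour, and the protocol discussion aims the combination at the metastases. This stands. An extrahepatic response is a legitimate endpoint if it is labelled as one, and different lesion scope in CR/PR and PD is an overlap without a precedence rule rather than a contradiction. The literal conflict is between the two new-lesion items.

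**The consequences are limited.** OS is untouched, and in a double-blind trial random misreading should not by itself favour an arm. Readers will also apply some sensible threshold to the liver. This stands in part. Blinding does not correct misclassification, and an unwritten threshold can differ between readers at the three sites.

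**Two stronger readings are tempting and not supported.** A reader might infer that ORR, DCR and PFS are not modified RECIST endpoints. The documents never state what those criteria require, and the reference list has no source for them, so a departure cannot be shown. What can be shown is that a named standard and a bespoke table coexist with nothing to say which governs. A reader might also infer that ORR is inflated by the share of responders with persisting liver tumour. That fails, because such a patient can remain a PR and other patients could be gained.

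**Conclusion.** The concern holds as an unreconciled and internally inconsistent response definition. Four defects are on the face of the table: CR and PR omit the liver while PD includes it; liver expansion has no threshold or reference scan; the 10 mm new-lesion limit is void; and CR and PR do not exclude PD. A fifth is that the table is not tied to the criteria named for the endpoints.

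Only CR has a known direction relative to whole-disease response: it can be overstated but not understated. The size and direction of any effect on ORR are unknown. The 75–96% false-progression range at the third scan rests on assumed independent continuous error and a reader who calls any increase expansion. It shows why a threshold is needed and does not estimate what happened in the trial. The documents give no measurement-error figure. This should be corrected for the secondary endpoints; the OS analysis does not depend on it.

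**What to change.** For endpoint derivation only:

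1. State which criteria govern PFS, ORR and DCR, and cite or set them out in the SAP.
2. If the table governs, report its results as extrahepatic ORR and extrahepatic DCR, not as overall modified RECIST response.
3. State that a scan meeting any PD criterion cannot count as CR, PR or SD.
4. Keep a single new-lesion rule.
5. State a quantified measure and a reference scan for intrahepatic growth, and say whether the expansion clause is confined to the liver.
6. Report PFS, ORR and DCR on all disease, intrahepatic and extrahepatic, as a labelled sensitivity analysis. Outcome results already accompany the plan, so replacing the main rule now would be post hoc.

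Progression is also a discontinuation reason in protocol Study Design, so that section and the table must be reconciled. No treatment rule is proposed here.

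**Cost:** wording, plus re-derivation from the 4-weekly scans already scheduled. Nothing shows that liver diameters were recorded, so existing scans may have to be re-measured. Reported response and progression figures may change.

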Subjects will be evaluated for tumor response every 4 weeks. Tumor imagine evaluation will be performed by either computerized tomography (CT) scan or MRI. Progression will be determined based on modified RECIST criteria for HCC. Drug therapy will be continued until unacceptable toxicity or disease progression occurs. If investigator determines the subject is benefiting from the blinded study drug and the subject is willing to continue the blinded study drug, the treatment may be continued beyond radiographic progression. Choice of subsequent therapies in case of progressive disease will be at the best discretion of the investigator, which should be beneficial to subjects overall. Subsequent treatments for HCC will be collected in the follow-up period. Requests for un-blinding will only be granted for emergency medical management. Subjects who have discontinued study therapy due to study drug toxicity or any reason other than confirmed tumor progression will continue to have tumor assessments every 4 weeks until documented radiographic tumor progression. All randomized subjects will be followed for overall survival until the required number of events has been reached.

Discontinuation of Subjects from Treatment: subjects must discontinue the investigational agents for any of the following reasons:

1. Withdrawal of informed consent (subject’s decision to withdraw for any reason).
2. Any clinical adverse event (AE), laboratory abnormality or intercurrent illness which,
3. in the opinion of the investigator, indicates that continued participation in the study is not in the best interest of the subject.
4. Pregnancy.
5. Loss of ability to freely provide consent due to either a psychiatric or physical (e.g. infectious disease) illness.
6. Disease progression*

* Note: If investigator determines the subject is benefiting from the blinded study drug (for example: subject may be experiencing symptomatic improvement at the time of documented radiographic progression) and the subject is willing to continue the blinded study drug, the treatment may be continued beyond radiographic progression.

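### Growth of existing liver lesions counts as progression with no threshold, reference scan or confirmation, so on a literal reading measurement variation can create PFS events and some DCR failures

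*Combined protocol and SAP*

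**What the plan says.** The response definitions stand in a table under protocol section 7.3. The progressive-disease row lists several routes joined by OR.

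- The first route is numeric: "Increase of > 20% in the SLD of extrahepatic metastatic lesions taking reference the smallest SLD of target lesions recorded since the treatment started". It adds a dating rule for an increase seen on two consecutive assessments.
- The last route concerns the liver: "Appearance of more intrahepatic lesions, expanding existing lesions (including portal vein emboli". It gives no percentage, millimetre limit, reference scan or confirmation.

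The row feeds two secondary endpoints. In protocol 7.2, "PFS is defined as the time (in months) from randomization to the time of radiographic disease progression", and "DCR is defined as the proportion of randomized subjects in each treatment arm whose best response is a CR, PR or SD". Stable disease is a residual class with no minimum duration: "Failure to meet criteria for complete or partial response, in the absence of progressive disease".

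The Study Design section points to another source: "Progression will be determined based on modified RECIST criteria for HCC". Protocol 7.2 and SAP 4.2 name the same criteria for ORR and DCR. Their thresholds are not reproduced, and no text ranks them against the table. SAP 4.2 and 5.2 add no rule for liver lesions.

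On timing, "Subjects will be evaluated for tumor response every 4 weeks", and the schedule of events shows imaging at M1 to M12.

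**The concern.** Two kinds of lesion in one row are held to different standards. Extrahepatic growth has to clear a margin that absorbs much of the reading error. Growth of an existing liver lesion or portal vein thrombus has no margin, so taken at its word any larger reading is progression. Each 4-weekly scan then gives a stable lesion another chance to be called progressive.

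At stake is the meaning of PFS in patients with intrahepatic disease. Event dates would partly reflect reading error, scan frequency and each reader's private idea of growth. Some stable patients would also be lost from DCR. Since the documents name a second set of criteria without ranking the two, sites could apply different rules.

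**Working it through.** **The plan's own figures.** The plan gives no figure for this point: no PFS or DCR rate, no reading error, no share of patients with liver lesions. Its one design figure, 106 patients, concerns OS. It can be reproduced with Freedman's formula: HR = 8.2/14.9 = 0.550; events = (1.960 + 0.842)² × (1.550/0.450)² ≈ 93.3, taken as 94, or 47 per arm; 47/0.9 = 52.2, taken as 53 per arm, 106 in total. It does not depend on the response table.

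**Exact result on the literal reading.** Take one truly stable lesion, independent and unbiased readings, and no ties.
- Against baseline, no false call by scan m requires baseline to be the largest of m + 1 readings. P(false PD by scan m) = m/(m + 1): 1/2 at scan 1 and 3/4 by scan 3.
- Against nadir, no false call requires every reading to fall below the one before. P = 1 − 1/(m + 1)!: by scan 3, 1 − 1/24 = 96%.

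**With rounding.** Assumptions, none from the documents: true diameter 50 mm, readings rounded to 1 mm, reading CV 3, 5 or 10%, and baseline included in the nadir. Rounding creates ties, which lowers the exact values. Simulated false PD for one stable lesion:

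| Rule | Time | CV 3% | CV 5% | CV 10% |
|---|---|---|---|---|
| Any increase, from baseline | by scan 3 | 66–73% across the three CVs | | |
| Any increase, from nadir | by scan 3 | 89–94% across the three CVs | | |
| Increase above 5 mm, from nadir | scan 1 | 0.5% | 6% | 22% |
| Increase above 5 mm, from nadir | by scan 3 | 3% | 25% | 65% |
| Increase above 20%, from nadir | scan 1 | 0% | 0.5% | 10% |
| Increase above 20%, from nadir | by scan 3 | 0% | 3% | 37% |
| Increase above 20%, from nadir | by scan 6 | 0% | 8% | 69% |

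Summing three such lesions with independent errors lowers the 37% at CV 10% to about 7%.

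**DCR.** It uses best response, and stable disease needs no minimum duration, so a patient read as stable at week 4 keeps disease control whatever follows. Only a progression call at the first scan counts, assuming that later assessments do not replace it. For any increase, this is 41–48% with one lesion and 45–49% with three lesions summed; the no-ties limit is 50%. It is 79–86% only if any one of three lesions, judged separately, is enough.

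**Direction of effect on PFS.** Let h < 1 be the true hazard ratio, and let false progression add the same hazard f (as a multiple of the control hazard) to both arms. The observed ratio is (h + f)/(1 + f), which exceeds h and moves toward 1 as f grows. The documents give no f, so the amount of dilution cannot be stated.

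**The case against.** The strongest reply is that the plan names modified RECIST for HCC as the basis for progression, so the bullet may be shorthand and readers may apply proper thresholds to the liver. Trained readers also rarely call a 1 mm change growth. This stands in part. The high figures need a reader who counts any measured increase, and a 5 mm tolerance lowers them sharply at low CV. It does not close the gap: the table is the only working definition supplied, and nothing says that the named criteria override it.

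It is also fair that the numeric rule is no cure. At CV 10% with a single lesion it still gives 37% false progression by scan 3.

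A reader might infer three stronger things that the documents do not support.
- That reading error does turn most stable livers into both PFS events and DCR failures. For PFS, a majority requires the literal reading and two or three scans. For DCR it is under half at the first scan for one lesion or a sum, and later scans do not matter. Patients without intrahepatic disease are untouched by the growth clause.
- That the bullet cancels the 20% rule for extrahepatic lesions. The wording is loose, but the clause follows new liver lesions and mentions the portal vein, and extrahepatic disease has its own routes.
- That the result is biased toward one arm or that the primary result is compromised. Assignment is blinded, so misclassification should be similar in the two arms, and OS does not use the response table.

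**Conclusion.** The defect holds in conditional form. The criterion for existing liver lesions lacks a threshold, a reference scan and confirmation, and its relation to modified RECIST is unresolved. On the literal reading, measurement variation alone can date PFS events in patients with stable intrahepatic disease, and it can cause some DCR failures at the first scan. The size depends on reading error, lesion size and number, and reader tolerance. All of these are assumptions here, so the figures show how sensitive the endpoint is and do not estimate what happened in the trial. The point concerns secondary endpoints and deserves correction because the remedy is cheap and already stands in the same row.

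**What to change.** For the derivation of PFS and DCR:
1. State that the last bullet applies to the liver only.
2. For existing intrahepatic lesions, use the threshold and reference of the first bullet: more than 20% growth in the sum of longest diameters over the smallest recorded sum.
3. State in protocol 7.2 and 7.3 and in SAP 4.2 whether the table or modified RECIST for HCC prevails for liver lesions, and make the passages agree.
4. State how portal vein thrombus is classified for the endpoints. No criterion is proposed here.

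The Study Design section also lists progression as a reason to discontinue treatment, with an exception for patients judged to benefit. That use must be reconciled with the table; this point proposes no rule for stopping treatment.

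The cost is rewording one bullet, a sentence on precedence, and one extra liver sum recorded from each existing scan. The downside is that some true liver progressions will be dated one scan later.
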